## Abstract

In Samoa, adult Type 2 diabetes prevalence has increased within the past 30 years. Patient preferences for care are factors known to influence treatment adherence and are associated with reduced disease progression and severity. However, patient preferences for diabetes care, generally, are understudied, and other patient-centered factors such as willingness-to-pay (WTP) for diabetes treatment have never been explored in this setting. Discrete Choice Experiments (DCE) are useful tools to elicit preferences and WTP for healthcare. DCEs present patients with hypothetical scenarios composed of a series of multi-alternative choice profiles made up of attributes and levels. Patients choose a profile based on which attributes and levels may be preferable for them, thereby quantifying and identifying locally relevant patient-centered preferences. This paper presents the protocol for the design, piloting, and implementation of a DCE identifying patient preferences for diabetes care, in Samoa. Using an exploratory sequential mixed methods design, formative data from a literature review and semi-structured interviews with n = 20 Samoan adults living with Type 2 diabetes was used to design a Best-Best DCE instrument. Experimental design procedures were used to reduce the number of choice-sets and balance the instrument. Following pilot testing, the DCE is being administered to n = 450 Samoan adults living with diabetes, along with associated questionnaires, and anthropometrics. Subsequently, we will also be assessing longitudinally how preferences for care change over time. Data will be analyzed using progressive mixed Rank Order Logit models. The results will identify which diabetes care attributes are important to patients (p < 0.05), examine associations between participant characteristics and preference, illuminate the trade-offs participants are willing to make, and the probability of uptake, and WTP for specific attributes and levels. The results from this study will provide integral data useful for designing and adapting efficacious diabetes intervention and treatment approaches in this setting.

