### Choice set design, and preference elicitation

A ‘Best-Best’ DCE was constructed (*preference elicitation)*. Best-Best DCEs elicit additional preference information, are designed to inherently rank choices, and increase the statistical power for analyses [72–74]. Participants are being presented with a series of choice sets, each with three different alternative care profiles (one of which will always be an ’opt-out/none of these’ for each attribute). Each profile presents a hypothetical scenario (comprised of combinations of attributes and levels) for diabetes care. Participants are asked to choose their most preferred option from the three profiles, followed by their second preference (but not worst) from the remaining alternatives. Because treatment protocols vary by patient, it was challenging to identify a true ’standard care’ level for each attribute. Frequently cited experiences (e.g., only being able to see the first available doctor) were included as potential levels in the design of the instrument and are intended to represent attribute levels generally (but not inclusive to all) experienced by patients. Our aim in doing so is to facilitate a comparison of the preferences for alternative options compared to these commonly experienced encounters; additionally, the inclusion of an opt-out option, provides better representation of real-world scenarios [72].

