### Planned statistical analyses

The statistical modeling of the DCE will be based on random utility theory, where participants choose between alternative profiles, and the attribute levels of the favored option is associated with the highest utility (benefit) to the specific participant [79]. A mixed logit model will be used to estimate choice models from the ’first best’ data and to observe the direction of the rank-ordered attribute choices [74, 80]. Rank order logit (ROL) modeling or Exploded Logit Modeling [81–83] will be used to observe a full ranking of the alternatives in all choice-sets (including first-best and second-best options in the same model) [74] and determine the probability that a participant chooses one option over the others, based on the chosen option’s attribute levels, while controlling for random factors and interindividual tastes [26, 71]. These types of analyses are useful for identifying unknown/unobserved heterogeneity of preferences [26, 73, 84] and will allow for analysis of the cross-sectional panel-like data (participants will be completing multiple choice sets and there will be multiple responses per case/participant). Progressive mixed ROL models will be constructed [74]. A mixed logit version of the ROL will be estimated by ’exploding’ the data as outlined in Lancsar et al. (2017) [72]. Briefly, this procedure will allow each choice set to result in five rows of data, with the first three rows (first sub-choice set) indicating the first-best preference (coded as 1, the remaining two alternatives as 0) and the remaining two rows (second sub-choice set) indicating the second-best preference (coded as 1, the remaining alternative as 0) [72]. By organizing the data in this manner, a traditional mixed multinomial logit model can be conducted that assesses the ranked choices [72]. The chosen profiles will be the dependent variable, and the levels of the attributes will be the independent variables (standard care attribute levels will be initially coded as the reference variable). Interaction terms will be introduced in Model 2 to estimate any associations between attributes and sex. Other case-specific characteristics (e.g., age, levels of diabetes knowledge, weight status, etc.) will be interacted with the intercept and selected attributes to explore the effect of participant characteristics on preferences in Model 3. [74]. We plan to use dummy coding (rather than effects level coding) for categorical variables to facilitate ease of interpretation [73, 74, 85]. The models will allow for the identification of which attributes are important (βs with p<0.05; Aim 2), the direction of that importance (positive or negative βs), and the relative importance of attribute levels compared to others (ratio of estimated parameter to relevant comparator; Aim 2). Further, we will be able to illuminate the trade-offs participants are willing to make between attributes, including marginal WTP (Aim 3). Because we will be including cost of treatment as an attribute, we can estimate the marginal WTP for other attributes; generally, marginal WTP can be estimated by dividing the estimated utility coefficient of an attribute by the utility coefficient of the cost of treatment attribute, holding other attributes constant [9, 86]. We will also be able to estimate the probability of participants taking up a care profile with specific attributes [26]. Sensitivity analyses will be undertaken if we suspect that the relative marginal utility of attributes varies due to differences in income levels. This may include exploring whether preference weights, probability of uptake of alternatives, and WTP vary by different income levels (Satisfaction from the attribute may be based on its associated costs; e.g., perceived satisfaction/preferences of care options may differ by participants’ ability to pay compared to their peers) [84, 87]. The distribution (level balance) of the attributes will be checked across the first and second preferred profiles to ensure the DCE is balanced and that logit model properties are met [88, 89].

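### Attribute importance (Aim 2) is decided from single level coefficients at p<0.05, so the error rate rises with the number of levels and the answer depends on the reference level

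*Protocol article*

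**What the plan says.** In Planned statistical analyses the criterion for Aim 2 is: "The models will allow for the identification of which attributes are important (βs with p<0.05; Aim 2". The Abstract repeats it at the level of the attribute: the results will "identify which diabetes care attributes are important to patients (p < 0.05".

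The same section fixes the coding: "We plan to use dummy coding (rather than effects level coding) for categorical variables to facilitate ease of interpretation". It sets the reference in these words: "standard care attribute levels will be initially coded as the reference variable". Choice set design, and preference elicitation gives every attribute 3 to 6 levels and names cost as the continuous attribute.

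On standard care, that section says: "Because treatment protocols vary by patient, it was challenging to identify a true" standard-care level for each attribute. Frequently cited experiences were used as levels instead, and these "are intended to represent attribute levels generally (but not inclusive to all) experienced by patients".

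No joint test of an attribute's levels is named. The Chow test analogue compares timepoints only.

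**The concern.** Aim 2 is a claim about attributes, but the criterion tests levels. With dummy coding, an attribute with L levels has L − 1 coefficients, each a contrast with one reference level. If one significant coefficient is enough, a six-level attribute has five chances at p<0.05 and a three-level attribute has two. The study is meant to say which attributes matter, so unequal error rates between attributes bear directly on its main result.

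The criterion also depends on the reference. Making another level the reference changes every contrast, so the same data can give a different answer for the attribute. That matters more when the choice of reference is described as an initial one.

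**Working it through.** **The plan's own figure.** Sample size and power gives N ≥ 500c/(T × A) with c = 6, T = 8 and A = 3. So N = 500 × 6 / (8 × 3) = 125, which reproduces the stated minimum. The formula contains no significance level or power, so it does not bear on this point.

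**Inputs from the article.** There are seven attributes with 3 to 6 levels each, dummy coding, a threshold of p<0.05, and cost as a continuous attribute.

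**Assumptions.**
- Tests are two-sided with critical value 1.96, since the article is interested in coefficients of either sign.
- Cost enters linearly and the other six attributes are categorical.
- Precision is equal for all levels of an attribute. The article's statement that levels appear equally often makes this reasonable.
- The number of levels of each attribute is not in the text shown, so the whole range from 3 to 6 is given.

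**Error rate for an attribute with no effect.** With equal precision, the standardised contrasts that share a reference are correlated 0.5. The chance of a false flag is 1 − P(all L − 1 contrasts lie within ±1.96), found by simulation with 2,000,000 draws. The independence value 1 − 0.95^(L−1) is shown for comparison.

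| Levels | Coefficients | False flag, correlation 0.5 | If independent |
|---|---|---|---|
| 3 | 2 | 9.1% | 9.8% |
| 4 | 3 | 12.6% | 14.3% |
| 5 | 4 | 15.6% | 18.5% |
| 6 | 5 | 18.2% | 22.6% |

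A linear cost term has one coefficient and stays at 5%. A joint test on L − 1 degrees of freedom holds 5% whatever L is.

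**Dependence on the reference.** Level utilities are in units of the standard error of one level. The any-coefficient rule was simulated with 400,000 draws. The power of the joint Wald test comes from the noncentral chi-square distribution with noncentrality Σ(u − ū)².

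- Three levels at −2, 0, +2 (noncentrality 4 + 0 + 4 = 8, 2 degrees of freedom): the any-coefficient rule detects the attribute in 82% of cases with an end level as reference and about 56% with the middle level. The joint test gives 72% with either.
- Six levels at −2, −1, −0.3, 0.3, 1, 2: the any-coefficient rule ranges from 64% to 88% according to the reference. The joint test gives 69% throughout.

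**The case against.** **The word any is not in the article.** True. The article speaks only of coefficients with p<0.05, and part of the same sentence concerns levels. But it names attributes as what is identified, and the Abstract does so too. Requiring every coefficient to be significant would make the criterion stricter as levels increase, and it would still depend on the reference.

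**The reference has a purpose.** The first research question, in DCE instrument construction, asks how preferred attributes compare with what standard care offers. Contrasts with a commonly experienced level answer that directly, and a joint test does not. This stands, and it is why the single coefficients should be kept. It does not make them a test of the attribute.

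**A separate analysis plan may add joint tests.** It may. But the criterion printed here is itself a rule about attributes, and followed as written it misses 5%.

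Four stronger conclusions that a reader might draw are not supported:

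- *No standard-care level could be identified.* The article says only that this was challenging, and it gives a substitute. The levels themselves are in S1 Table, which is not shown. What remains is that the reference is provisional.
- *The study as a whole has a very high false-positive rate.* If all seven attributes had no effect and were independent, the chance of at least one false flag would be 1 − (1 − 0.0908)^6 × 0.95 = 46% with three levels throughout, and 1 − (1 − 0.1824)^6 × 0.95 = 72% with six. The attributes were chosen because they were the most frequently reported, so no effect anywhere is not a realistic basis. The per-attribute figures are the ones to use.
- *The joint test always has more power.* It does not: 72% against 82% with an end level as reference in the three-level example. Its merits are the 5% rate and invariance to coding.
- *Multiplicity correction across attributes is required.* Seven unadjusted joint tests would still give 1 − 0.95^7 = 30% for at least one false flag if independent and all null. Whether a preference survey needs familywise control is debatable, and this point does not demand it. Nor does it ask for ranking by utility range, which itself favours attributes with more levels.

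**Conclusion.** The point holds in a limited form. The stated criterion judges attributes by level coefficients. Read as any significant coefficient, it gives a false-positive rate of about 9% to 18% per categorical attribute, rising with the number of levels, in place of 5%. Whether a real effect is detected also depends on a reference level that is set only initially. The exact rates rest on equal precision per level and on the any-coefficient reading; the direction does not depend on the precise values.

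The level-versus-reference contrasts are valid as statements about levels. Marginal willingness-to-pay estimation, the sample-size figure and the linear cost attribute are unaffected.

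**What to change.** In Planned statistical analyses, and correspondingly in the Abstract:

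1. Declare an attribute important by one joint Wald or likelihood-ratio test of all its level coefficients.
2. Name the reference level of each attribute, the commonly experienced one, before analysis, and remove the provisional wording.
3. Keep the single-level coefficients, with confidence intervals, as level-versus-reference comparisons for the first research question.

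This costs a few sentences and one post-estimation command per attribute, with no new data. The downside is that an attribute flagged by a single level may no longer be called important, and for some reference choices the joint test detects a real effect less often than the any-coefficient rule would.

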**Fig 1 pone.0295845.g001:**
[figure not shown]
Exploratory sequential design.

The aims of this project are:

To design, pilot, and implement a DCE measuring diabetes care preferences in Samoa.To identify and measure the strength of preference and importance of attributes of diabetes care alternatives and standard care options.To identify the trade-offs (i.e., marginal Willingness to Pay (WTP)), participants are willing to make to obtain preferred attributes, and the probability of uptake for such services.To measure longitudinal changes in care preferences over time.

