To design the alternative profiles for both the pilot and final instrument, we mirrored similar DCEs utilized elsewhere and included 8 of the most frequently reported attributes (garnered from the literature review, interviews, and consultation) in the instrument (DCEs within health economics are estimated to have a mode of 6 attributes but can range from 2–24 [31]). The eight attributes included in the pilot was reduced to seven following refinements. Each attribute is between 3–6 levels. The chosen attributes and levels were entered into JMP^®^ Pro 15 (SAS Institute Inc., Cary, NC) where we specified the creation of 12 choice sets for the pilot, and 8 choice sets for the final baseline DCE [71]. Limiting the number of attributes, levels, and choice sets was undertaken to prevent participant fatigue and reduce cognitive burden [32, 73]. We utilized a fractional factorial design [26, 31, 32] to reduce the high number of possible combinations of attributes and levels that could be included in each choice set and an efficiency design to maximize precision [23, 75] (*experimental design*). Both the pilot and final DCE included continuous (i.e., costs of treatment) and categorical attribute levels. Attribute levels are balanced and appear an equal number of times (reducing bias). Further, JMP software allows for the randomization of the order of the choice sets that are presented to the participants and for the creation of multiple survey blocks (we created 9 survey blocks). This helps to ensure the random elicitation of choice sets (reducing bias) and increases the diversity of attribute and level combinations that are encountered by the participants. Block assignments will be adjusted for during analysis.

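### The only stated estimator of marginal willingness to pay omits the minus sign, so every estimate has its sign reversed if the formula is followed as written

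*Protocol article*

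**What the plan says.** The third aim listed under Aims and hypotheses is "To identify the trade-offs (i.e., marginal Willingness to Pay (WTP)), participants are willing to make to obtain preferred attributes". The Planned statistical analyses section names the estimator for it. It opens with "Because we will be including cost of treatment as an attribute, we can estimate the marginal WTP for other attributes; generally, marginal WTP" and then gives the rule: "marginal WTP can be estimated by dividing the estimated utility coefficient of an attribute by the utility coefficient of the cost of treatment attribute", with the other attributes unchanged. No other WTP formula appears in the article.

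Three further statements bear on how the rule would work:

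- Cost is a numeric attribute. The section on choice set design says: "Both the pilot and final DCE included continuous (i.e., costs of treatment) and categorical attribute levels".
- Coefficient signs carry meaning. The analysis section will read from the models "the direction of that importance (positive or negative βs", so a positive coefficient marks a preferred level and a negative one a level that patients would rather avoid.
- The coefficients come from mixed rank-ordered logit models: "Progressive mixed ROL models will be constructed", and "A mixed logit version of the ROL will be estimated by ’exploding’ the data".

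The article does not say that cost is entered as its negative, or that absolute values are taken.

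**The concern.** In a random utility model, a higher price normally lowers utility, so the cost coefficient is negative. A positive coefficient divided by a negative one is negative. The written rule therefore gives a negative WTP to care that people want and would pay for, and a positive WTP to features that they dislike.

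Categorical attributes are to be dummy-coded against standard care levels. A level preferred to standard care would thus be reported as one that patients must be compensated to accept.

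WTP is an aim in its own right. The Introduction promises it to the health system, and the Discussion describes the WTP estimates as relevant to policy. A table with its signs reversed would point a payer in the wrong direction. The planned comparison of WTP across income levels would be reversed as well.

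**Working it through.** The article states no WTP figure and no coefficient, so there is no figure of its own to reproduce on this point. The check is algebra plus an illustration with assumed values.

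**Inputs**

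- From the article: the ratio of attribute to cost coefficient, with no minus sign; cost as a continuous attribute; a positive coefficient meaning preferred.
- Assumed: the cost coefficient is negative (the usual expectation from utility theory, which the article does not state). Attribute coefficients of 0.5 and 0.6 and cost coefficients of -0.02 and -0.05 per currency unit are illustrative.

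**Algebra**

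1. Write the part of utility that matters as U = b·x + c·cost, with x an attribute level (0/1 for a dummy) and c < 0.
2. Marginal WTP is the rise in cost that exactly offsets a gain of one unit in x: b + c·Δcost = 0.
3. Hence Δcost = -b/c. The article's rule gives b/c, which is the same number with the opposite sign.

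**Illustration over the assumed values**

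| b | c | Rule as written, b/c | Marginal WTP, -b/c |
|---|---|---|---|
| 0.6 | -0.02 | 0.6/(-0.02) = -30 | +30 |
| 0.5 | -0.02 | 0.5/(-0.02) = -25 | +25 |
| 0.6 | -0.05 | 0.6/(-0.05) = -12 | +12 |
| 0.5 | -0.05 | 0.5/(-0.05) = -10 | +10 |
| -0.6 | -0.02 | -0.6/(-0.02) = +30 | -30 |

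The absolute value is the same in every row and only the sign differs. The last row is a disliked level, which the rule turns into something patients appear willing to pay for. The first two rows show the effect on ordering. The level worth more (30 against 25) comes out lower (-30 against -25), so rankings on signed values are reversed too.

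The result does not depend on the chosen values. It holds for any negative c. A confidence interval (L, U) for b/c becomes (-U, -L) for -b/c, so its width and the test against zero are unchanged.

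**The case against.** The strongest reply is that the sentence is a loose description in prose. It is qualified by words to the effect of generally and can be, it cites sources that are not shown here, and it is not set out as a computing rule. The authors will already have read the signs of the coefficients before they form any ratio. A table in which every preferred level has a negative WTP would be noticed at once. Magnitudes, significance and ranking by absolute size do not depend on the sign. Sample size, design and model fit do not depend on it either, and the repair can be made at any time before reporting.

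Most of this stands, and it limits the weight of the point. It does not make the sentence right. This is the only estimator given for a named aim, and nothing in the article supplies the missing sign.

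A reader might infer something stronger: that a plain ratio is invalid or undefined because the coefficients come from a mixed model. The article does not support that. It says of these analyses that "These types of analyses are useful for identifying unknown/unobserved heterogeneity of preferences", but it does not say which coefficients are random or with what distribution, and it never says that cost is random. The consequences differ by specification (assumed mean coefficients 0.5 and -0.05, so the ratio of means with the correct sign is 10):

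- **Cost fixed, attribute normal with SD 0.5.** WTP has mean 0.5/0.05 = 10 and SD 0.5/0.05 = 10. The ratio of means is the mean WTP.
- **Cost log-normal in absolute value.** Mean WTP is finite but exceeds the ratio of means by the factor 1 + CV². At CV 0.25, 0.5 and 1 it is 10.6, 12.5 and 20.0.
- **Cost normal.** The ratio has no finite mean. At CV 0.5 and 1, the share of the cost distribution at or above zero is P(Z > 2) = 2.3% and P(Z > 1) = 15.9%.

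The difficulty thus needs a random cost coefficient, and an undefined mean needs one with density at zero. The first case is fully compatible with the article. The choice of random parameters, their distributions and the interval method are details that an article commonly leaves to the full protocol or analysis plan, so their absence is not a finding.

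**Conclusion.** The sign point holds. The marginal WTP rule in the Planned statistical analyses section is wrong as written: with the expected negative cost coefficient, it reverses the sign of every WTP estimate and leaves the absolute size unchanged (-30 in place of +30 with the assumed values 0.6 and -0.02).

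This rests on two assumptions. Cost is coded in its natural direction, with a higher value meaning a higher price, and its estimated coefficient is negative. The article says nothing against either.

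The weight is minor to moderate. It concerns the only stated estimator for Aim 3, but the sentence is a general description, the error is easy to see in the results, and no design decision depends on it.

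**What to change.** In the Planned statistical analyses section, write marginal WTP = -(attribute coefficient)/(cost coefficient). Alternatively, keep the ratio and state that cost enters the model as its negative. Only one of the two should be adopted, because applying both would reverse the sign again.

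The change is one line. It needs no new data, no change to the survey, sample size or models, and has no statistical downside.

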### Implementation

The finalized DCE instrument will be administered to n = 450 adult Samoans recently diagnosed with diabetes (data collection started August 2023; funded as an aim of 5K01DK132514: The Diabetes Clinical outcomes Associated with Retention and Engagement in Care, in Samoa (Diabetes CARE); PI: [name]). After obtaining written informed consent from all participants, RAs are explaining the study objectives, describing what a DCE is (i.e., an explanation that the presented choice sets represent hypothetical scenarios), and are consistently describing the intended definitions of the included attributes and levels. This latter step is intended to help participants assess levels that may be subjective or unfamiliar. For example, continuous glucose monitoring is an included attribute level. This type of glucose management is not common in Samoa at this time, and further explanation may be needed for some participants [33]. In addition to administering the DCE, RAs are collecting demographic (i.e., sex, age, region of residence), anthropometric (i.e., weight and height, and blood pressure), health, and socioeconomic data (income and assets) from participants. Participants are also being administered diabetes knowledge [77], self-management and distress, and treatment adherence [78] questionnaires. These data will be used to examine whether attribute preferences vary by sex and/or are associated with chronic disease risk, age, socioeconomic position, or levels of diabetes knowledge. Assessments take approximately 30–40 minutes.

Two hundred and twenty participants will be asked to complete additional DCEs at 12- and 24-months post initial assessment. The same DCE instrument will be used to measure how preferences change over time as individuals live and manage their diabetes.

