
Few longitudinal studies using discrete choice experiments have been undertaken [90], therefore analyses will be largely exploratory. Because time between assessments (12 months) is short, the same DCE instrument will be used at each timepoint [90, 91]. Following best practices, we will analyze models at each timepoint using multinomial logit modeling [91]. The Chow Test Analogue for logistic regression will be used to test whether the models’ attribute coefficients significantly differ between timepoints. The Chow Test Analogue allows for comparative analysis of different regression models fitted to two different data sets [91]. By including demographic, socioeconomic, and care-related questionnaire data into our models, we will be able to explore how external factors, and especially changes in external factors such as income status, care use/disuse, and diabetes management and distress, are associated with changes in preferences over time. In the unlikely case that we experience greater loss to follow-up and attrition than expected, we will use repeated cross-sectional DCE approaches (such as a covariate extended model) to measure if differences in preferences across samples are significant [90]. Analyses will be completed in Stata v. 17 (College Station, TX) using the Choice Models (CM) suite of commands [92].

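### Minor: cost coefficients are to be compared across waves of an unchanged instrument with no stated price-level adjustment, so general inflation could pass for a small change in cost sensitivity

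*Protocol article*

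**What the plan says.** The Implementation section of the protocol article sets the follow-up: "Two hundred and twenty participants will be asked to complete additional DCEs at 12- and 24-months post initial assessment". It gives the purpose in the next sentence: "The same DCE instrument will be used to measure how preferences change over time as individuals live and manage their diabetes". The longitudinal paragraph of Planned statistical analyses repeats the reuse and gives the reason: "Because time between assessments (12 months) is short, the same DCE instrument will be used at each timepoint".

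On the cost attribute, the section on choice set design states: "Both the pilot and final DCE included continuous (i.e., costs of treatment) and categorical attribute levels". The levels themselves are in S1 Table, which is not part of the text at hand. Marginal willingness to pay (WTP) is obtained by "dividing the estimated utility coefficient of an attribute by the utility coefficient of the cost of treatment attribute, holding other attributes constant". That definition belongs to the main analysis and Aim 3.

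For change over time, which is Aim 4, separate models are fitted at each timepoint, and then: "The Chow Test Analogue for logistic regression will be used to test whether the models’ attribute coefficients significantly differ between timepoints". The article describes this work as follows: "therefore analyses will be largely exploratory". It names income status, care use, and diabetes management and distress as external factors to explore. The price level is not among them.

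**The concern.** An unchanged instrument presumably shows the same nominal amounts at every wave. Baseline interviews are expected to run from August 2023 to July 2024, so 24-month interviews would run to about July 2026. If prices rise meanwhile, a given amount is a smaller real cost at each later wave. Cost enters as a continuous attribute and its coefficient is among those compared. A general price rise would therefore be mixed with the time effect that Aim 4 is meant to measure, on this one attribute.

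The reason given for reuse, a short interval of 12 months, fits successive waves. It does not cover a comparison of the first wave with the last.

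At stake is the reading of the cost result. A smaller cost coefficient could be taken to mean that patients become less sensitive to cost as they live with diabetes, when only the price level has moved. If WTP were also recomputed by wave, every value would rise by the same factor. Reported income, one of the factors to be explored, is subject to the same drift if it is recorded in current money.

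**Working it through.** **The plan's own figures.** The article gives no figure on prices. Its one design calculation, the minimum sample size, reproduces as 500 × 6 / (8 × 3) = 125. It has no bearing on this point.

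**Inputs from the article.** Waves at baseline, 12 and 24 months; 220 participants in follow-up; 8 choice sets of two care profiles plus an opt-out; continuous cost; between-wave test on attribute coefficients.

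**Assumptions, because the article is silent.** Inflation of 2% to 8% per year, the same nominal cost levels at each wave, and respondents who judge cost in real terms.

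**Form of the effect.** Let P = (1 + annual inflation)^years, let b be the real cost coefficient and c the displayed amount.
- The cost part of utility at the later wave is b × (c/P) = (b/P) × c. A model fitted on c therefore returns b/P.
- The coefficient of any other attribute, a, is unchanged.
- WTP in absolute value is a/b at baseline and a/(b/P) = P × a/b later.

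**Size.**

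| Assumed inflation | Interval | P | Cost coefficient (1/P − 1) | Nominal WTP, if recomputed (P − 1) |
|---|---|---|---|---|
| 2% | 12 months | 1.020 | −2.0% | +2.0% |
| 8% | 12 months | 1.080 | −7.4% | +8.0% |
| 2% | 24 months | 1.02² = 1.040 | −3.9% | +4.0% |
| 8% | 24 months | 1.08² = 1.166 | −14.3% | +16.6% |

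**Would the planned test see it?** This was approximated from the expected information of a conditional logit with 220 people per wave and 8 sets each. Further assumptions were:
- 21 parameters: 19 dummies from six categorical attributes with 6, 5, 4, 4, 3 and 3 levels, plus cost and an opt-out constant;
- a cost coefficient of −0.5 to −2 over the full cost range;
- independent waves and a two-sided 5% level.

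Example with a cost coefficient of −1, 5% inflation, 24 months and first choices only: the shift is 1 × (1 − 0.907) = 0.093. The standard error per wave is 0.102, so that of the difference is 0.102 × √2 = 0.144. The ratio is 0.093/0.144 = 0.65, and the chance of significance is about 10%.

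The chance that a 24-month inflation shift alone is significant, over first-choice and full-ranking data and over the three cost coefficients tried (−0.5, −1, −2), is:

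| Assumed inflation | Test of the cost coefficient alone | Joint test of all 21 coefficients |
|---|---|---|
| 3% | 6–14% | 5–9% |
| 5% | 6–30% | 5–19% |
| 10% | 10–76% | 6–70% |

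The 10% row lies above the assumed range and bounds its upper end. The waves share participants; if their answers are positively correlated, the difference would be estimated more precisely and these chances would be somewhat higher.

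**Effect of deflating.** If respondents judge cost in real terms, fitting on c/P returns b at every wave and the shift is zero at any inflation rate. If they react to the nominal amount, utility is b × c = (b × P) × (c/P). The deflated model would then show a spurious increase of P − 1, which is 4.0% to 16.6% at 24 months. Neither version is right under both behaviours.

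**The case against.** The strongest reply is that nothing in the design is wrong. Holding the levels constant is what makes waves comparable, and how a covariate is scaled for analysis is the kind of detail that a condensed article may leave to a fuller plan. That stands in part, and it is a main reason to rate the point as minor. It does not dispose of the point. The article fixes the reuse, the reason for it and the test, and followed as written these mix the price level into the time effect on cost.

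Other replies carry weight:
- The reason about 12 months is accurate for adjacent waves, and the article does not fix which pairs are compared. For adjacent waves only the 12-month sizes apply.
- The single direction of the effect needs respondents who judge cost in real terms and an ability to pay that keeps up with prices. If incomes lag, cost sensitivity could stay flat or rise.
- Deflation is itself a modelling assumption, as the working shows.
- The planned look at income change covers ability to pay in part, but not the price level.
- The longitudinal analysis is presented as exploratory, and at low inflation the shift would seldom reach significance. That limits false positives. It does not remove the shift from the point estimates.

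A reader might go further and infer that reusing the instrument is a mistake, or that inflation will distort WTP and the preference results as a whole. The documents do not support this. No comparison of WTP between waves is planned, the non-cost coefficients are unaffected, the cost levels are not shown, and no inflation rate is given.

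**Conclusion.** The point holds as a minor one, confined to the cost coefficient. No price-level adjustment is stated for a between-wave comparison that includes a continuous cost attribute shown in an unchanged instrument. To the extent that prices rise and respondents judge cost in real terms, the nominal coefficient is multiplied by 1/P. At an assumed 2% to 8% per year that is about −2% to −7% over 12 months and −4% to −14% over 24 months. Any WTP recomputed at a later wave would be multiplied by P.

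The conclusion rests on three assumptions that the article does not settle: the inflation rate, unchanged nominal levels in S1 Table, and real-terms judgement by respondents. With 220 participants the shift would often go undetected. The risk is therefore a misread point estimate more than a false significant test, unless inflation is high and cost weighs heavily in the choices.

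**What to change.** Leave the instrument and visits as they are. Where the cost coefficient, or WTP if it is computed by wave, is compared between timepoints:

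1. Fit the models as planned on the displayed amounts.
2. Fit them again with displayed cost and reported income divided by the official consumer price index for the interview month, scaled to 1 at a fixed baseline month. Using the interview month also handles the spread of interviews within a wave.
3. Report the nominal and constant-price results side by side.
4. Interpret a change in cost sensitivity as a change in preference only if it holds in both versions.

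State this rule before the waves are compared. The cost is one deflator built from the interview date and a published index, and one extra model per wave. The drawback is that the constant-price version assumes respondents judge cost in real terms, which is why it accompanies the nominal result and does not replace it.
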